### Statistical analyses

All analyses will be performed according to the intention-to-treat principle. Baseline characteristics of employees in the two groups will be compared using descriptive statistics. Linear and logistic regression will be performed. Furthermore, analyses at the level of the OHSs are performed by the use of multilevel analysis. To assess whether protocol deviations cause bias, the results of the intention-to-treat analyses will be compared to per-protocol analyses, from which employees who are not treated according to the procedure of the intervention. For all analyses, a two-tailed significance level of < 0.05 is considered statistically significant. Linear and logistic regression analyses will be performed with SPSS 18.0 (SPSS Inc. Chicago, Illinois, USA). The multilevel statistical analyses are performed with MIWin 2.0.

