### Randomization and stratification

All eligible participants will be randomly assigned to the intervention or the control group after the baseline measurements. To prevent an unequal distribution among groups, employees will be pre-stratified on two prognostic factors before randomization. The first one is requirement of hearing protection at the workplace. The second prognostic factor is psychosocial related problems based on the HDS (score of 3 or more on the three distress items (items 1 to 3) of the HDS). This results in a total of four strata. Furthermore, block randomization, with blocks of four, will be applied to ensure equal groups sizes within each stratum and for practical reasons. An independent statistician will prepare the randomization schedule by using computer-generated random numbers. The research assistant will arrange sealed envelopes before the start of the study containing either a referral to the intervention group or to the control group. When the baseline questionnaire is completed, the employee can choose an envelope in the correct stratum that contains the randomization under the researcher's supervision.

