### Sample size

'Need for recovery after work' is the primary outcome of this study and was therefore used for the power calculation. The 'need for recovery after work' scale comprises 11 dichotomized items [26]. Based on previous findings [12,27] the expected effect size is 0.40. To detect this effect size (assuming a two-sided significance level: 0.05, power (1-β): 80%) 63 persons per group are needed. Taking into account 20% loss to follow up, the required sample size is 160 persons in total, with 80 participants assigned to the control group and 80 participants to the intervention group.

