### Economic evaluation

In the economic evaluation the costs and consequences of the VEP integrated care programme and usual care will be compared. As mentioned in the introduction, hearing impairment has consequences with potentially substantial costs for the companies, as well for the society. Since interventions in occupational care in The Netherlands have to be paid by employers, the economic evaluation will be conducted from both a company and a societal perspective. From the societal perspective, all costs and consequences of the intervention will be taken into account regardless of who pays for them. From the company perspective, only costs due to the intervention, productivity, and sick leave will be taken into account.

Missing data will be imputed using a multiple imputation procedure according to the multivariate imputation by chained equations (MICE) method [50,51]. To calculate incremental cost-effectiveness ratios (ICER), the difference in mean costs between the intervention and control group will be divided by the difference in outcome measures between the two groups. Confidence intervals (95%) will be estimated using bias corrected and accelerated (BCA) bootstrapping [52]. The cost-effectiveness ratios will be graphically presented in a cost-effectiveness (CE) plane [53]. Cost-effectiveness acceptability curves (CEAC) will also be estimated [54].

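### The ICER is built from group differences with no baseline adjustment mentioned; adjusting it and the primary regression for baseline values and the strata is a free improvement

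*Protocol article*

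**What the plan says.** **Randomisation.** Under Randomization and stratification, "employees will be pre-stratified on two prognostic factors before randomization". Of these factors, "The first one is requirement of hearing protection at the workplace"; the second is a score of 3 or more on the three distress items of the screener. This gives four strata, with blocks of four.

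**Baseline data.** Table 2 schedules NFR, EQ-5D, sick leave, work productivity and health care use at T0 and at 3, 6, 9 and 12 months. The sick leave and health care questions look back three months.

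**Effect analysis.** Under Statistical analyses, baseline characteristics are compared descriptively. Then: "Linear and logistic regression will be performed". A multilevel analysis at the level of the occupational health service is added. No covariate is named and none is ruled out.

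**Economic evaluation.** The ICER is given as a formula: "the difference in mean costs between the intervention and control group will be divided by the difference in outcome measures between the two groups". Multiple imputation, BCA bootstrapping, the cost-effectiveness plane and acceptability curves are specified; adjustment is not mentioned. Under Health related quality of life, QALYs come from utilities linearly interpolated between measurements.

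**The concern.** The economic section sets out its estimator, and its plain reading is an unadjusted one. Stratification covers hearing protection and distress, not utility or costs, so nothing in the design limits chance imbalance in those two at T0. A QALY difference in a one-year trial can be small, and it is the denominator of a ratio, so a small accidental component can move the result.

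For the effect analysis, the randomisation balances two factors chosen as prognostic, but the article does not say that the model will use them or baseline NFR. If they were left out, precision would be lost and standard errors would be too large, because the balance achieved by design would not be reflected in the analysis.

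**Working it through.** **1. The plan's own figure.** Inputs from Sample size: "Based on previous findings [12,27] the expected effect size is 0.40". The section also gives a two-sided 5% level, 80% power, 63 per group before dropout, and 80 per group (160 overall) after allowing for 20% attrition.

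- n per group = 2 × ((1.960 + 0.842)/0.40)² = 98.1, so 99 (about 100 by the t distribution). The stated 63 is not reproduced. It matches an effect size of 0.50: 2 × (2.802/0.50)² = 62.8. That discrepancy is a separate finding; it is used here only to fix the starting power.
- Completers per group: 80 × 0.80 = 64.

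**2. Power with baseline adjustment.** Regressing follow-up NFR on arm and baseline NFR multiplies the residual variance by 1 − ρ², where ρ is the baseline-to-follow-up correlation. The article does not give ρ; 0.3 to 0.7 is assumed. Normal approximation:

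power = Φ( (0.40/√(1 − ρ²)) × √(64/2) − 1.96 )

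| ρ (assumed) | n per group for 80% power | Power with 64 per group |
|---|---|---|
| 0 (unadjusted) | 99 | 62% (61% by t) |
| 0.3 | 90 | 66% |
| 0.4 | 83 | 70% |
| 0.5 | 74 | 74% |
| 0.6 | 63 | 81% |
| 0.7 | 51 | 89% |

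Example, ρ = 0.5: 0.40/0.866 = 0.462; 0.462 × 5.657 = 2.613; Φ(2.613 − 1.960) = 0.743.

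Adjusting for the strata alone, with assumed R² of 0.05, 0.10 and 0.20, gives 64%, 66% and 72%.

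**3. Test level if the strata are ignored.** With arms balanced within strata that explain a share R² of the outcome variance, the usual standard error is too large by a factor 1/√(1 − R²). In large samples the true two-sided level is 2Φ(−1.96/√(1 − R²)):

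- R² = 0.10: 2Φ(−2.066) = 0.039
- R² = 0.20: 2Φ(−2.191) = 0.028

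Simulation of 160 participants in four balanced strata gave 0.039 and 0.031. R² is assumed. The error is on the conservative side.

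**4. Baseline utility in the QALY.** With measurements every 0.25 year and linear interpolation, the weights are 0.125, 0.25, 0.25, 0.25 and 0.125, summing to 1 year. For a chance T0 difference of 0.03 (assumed):

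- Direct part: 0.125 × 0.03 = 0.00375, about 0.004 QALY.
- With carry-over, assuming each later utility regresses on baseline with slope ρ: 0.03 × (0.125 + 0.875ρ). This is 0.012 at ρ = 0.3, 0.017 at 0.5 and 0.022 at 0.7.

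To place 0.03: the standard error of a baseline difference with 80 per group is SD × √(2/80) = 0.158 SD, so 0.03 is one standard error when the SD is about 0.19. The article gives no utility SD.

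**5. Baseline costs.** T0 costs cover the three months before randomisation, so they are not part of the follow-up total. An imbalance enters only through the correlation with later costs, for which the article gives no figure.

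**The case against.** A reader might infer that the effect analysis uses plain group differences and ignores baseline values and strata. The article does not support that. It announces regression, the usual vehicle for covariates, and neither lists nor excludes any. The sentence on descriptive comparison concerns the baseline table and does not limit the models. Psychosocial workload is called potentially prognostic for the primary outcome, which fits an intention to use covariates. A condensed article commonly leaves the covariate list to a fuller document, so on its own this part is missing detail, not error. This objection stands.

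The ICER sentence can also be read as the generic definition of the ratio, which adjusted differences would satisfy equally well. This stands in part: the sentence does not forbid adjustment, but it states how the ratio is formed, its literal reading is unadjusted, and the section describes its other methods in some detail.

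Randomisation keeps the unadjusted differences unbiased on average, and ignoring the strata makes the test conservative. Both points stand. A reader might suspect an inflated false-positive rate; the arithmetic shows the opposite.

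Finally, every magnitude rests on assumed values. At ρ = 0.3 the power gain is only 4 to 5 percentage points, and no decision threshold is given against which to judge 0.004 QALY. This stands, and it is why ranges are shown.

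**Conclusion.** The point holds as an improvement to the stated method. Its firmest part is the ICER: as written, chance imbalance in T0 utility enters the QALY difference directly with weight 0.125 year and further through later utilities, and imbalance in T0 costs enters through later costs. An imbalance of 0.03 would contribute 0.004 QALY directly and about 0.012 to 0.022 in all for assumed slopes of 0.3 to 0.7.

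For the primary analysis, the conclusion is only that the article does not name baseline NFR or the two strata as covariates. Naming them would raise power from about 61-62% to between 66% and 89% over assumed ρ of 0.3 to 0.7. Adjustment reaches 80% power at effect size 0.40 only if ρ is about 0.60 or more. It therefore cannot be relied on to repair the sample size, which needs its own correction. Nothing here makes the unadjusted analysis invalid.

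**What to change.** In Economic evaluation, state that the cost and effect differences forming the ICER are estimated by regression (seemingly unrelated regression would handle both together) on arm, baseline utility for QALYs or baseline NFR for the NFR-based ratio, baseline three-month costs, hearing-protection stratum and distress stratum. State that the bootstrap, the cost-effectiveness plane and the acceptability curves use these adjusted differences.

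In Statistical analyses, state that the primary model regresses follow-up NFR on arm, baseline NFR and both stratification factors, and that other outcomes measured at T0 are adjusted for their own baseline value. If a fuller document already says this, a sentence pointing to it is enough.

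The cost is wording only. Every variable is collected at T0 or used for randomisation. The covariate set should be fixed before allocation is revealed to the analyst.

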### Economic evaluation

In the economic evaluation the costs and consequences of the VEP integrated care programme and usual care will be compared. As mentioned in the introduction, hearing impairment has consequences with potentially substantial costs for the companies, as well for the society. Since interventions in occupational care in The Netherlands have to be paid by employers, the economic evaluation will be conducted from both a company and a societal perspective. From the societal perspective, all costs and consequences of the intervention will be taken into account regardless of who pays for them. From the company perspective, only costs due to the intervention, productivity, and sick leave will be taken into account.

Missing data will be imputed using a multiple imputation procedure according to the multivariate imputation by chained equations (MICE) method [50,51]. To calculate incremental cost-effectiveness ratios (ICER), the difference in mean costs between the intervention and control group will be divided by the difference in outcome measures between the two groups. Confidence intervals (95%) will be estimated using bias corrected and accelerated (BCA) bootstrapping [52]. The cost-effectiveness ratios will be graphically presented in a cost-effectiveness (CE) plane [53]. Cost-effectiveness acceptability curves (CEAC) will also be estimated [54].

### Process evaluation

Additional to the effect evaluation and the economic evaluation, the process of the VEP integrated care programme will be evaluated. Two models for process evaluation will be combined, namely the model of Steckler and Linnan [55] and the RE-AIM model [56,57]. In this study we will evaluate the following six components, which are derived from these two models; recruitment (procedures used to recruit employees for this study); context (characteristics of the participants and companies that affect the VEP integrated care programme); reach (number of participants reach for the HDS, participants who are willing to participate in the study and number of participants in the study groups); dose delivered (the amount of advices and recommendations delivered by the team of the VEP integrated care programme); dose received (the extent to which employees use advices and recommendations by the team of the VEP integrated care programme) and perceived effectiveness (participants' and professionals' view of effectiveness of the VEP integrated care programme for the participants). In addition, satisfaction of employees with the VEP integrated care programme is measured using a modified version of the Patient Satisfaction with Occupational Health services Questionnaire (PSQOH) [58]. Questionnaires for the process evaluation are assessed in the intervention group at three and six months after baseline.

## Discussion

Hearing impairment at the workplace has consequences for the hearing impaired individual, the company, and society [4,7]. So far, the majority of studies on the relationship between hearing impairment and work, published in the international literature, are restricted to the causes of noise-induced hearing loss, on how to protect employees from dangerous noise levels, and on the development of hearing protection programmes [18]. The specific problems in communicative function encountered by workers with hearing impairment in the workplace have rarely been addressed in research or in clinical practice protocols. Hétu et al. [9] argued that a multidisciplinary approach is crucial for a successful management of complex problems in the workplace. To the best of our knowledge, this is the first study that describes the evaluation of an integrated care programme for hearing impaired employees that targets both the individual capacities as well as the work environment according to a randomized controlled design.

The VEP integrated care programme is unique because usual care often does not include adequate interdisciplinary diagnostics and audiological rehabilitation procedure other than hearing aid fitting for addressing the problems related to hearing impairment in the workplace. In particular the psychosocial problems are often left behind and protocols for improvement of the workplace by applying accommodations for the hearing impaired employee are not broadly implemented.

Results of this study will be analysed within the context of the ICF classification. From the perspective of the society and employer the study will evaluate the components of the health condition (i.e., hearing impairment at the workplace) such as activities, participation and environmental and personal factors, namely with questionnaires about work demands, 'need for recovery after work', and general health status. In this article the design of a study to investigate the effectiveness, cost-effectiveness, and feasibility of the VEP integrated care programme for hearing impaired employees is described.

### Methodological considerations

A strength of the current study is the randomized design. Another strength is that not only the effects of the VEP integrated care programme will be evaluated, but also the cost-effectiveness and the process of the programme. Finally, in this study presenteeism is measured. This is important, because even if an employee is not absent from work, hearing impairment can cause a reduction of work productivity [14].

Hearing impairment is not a disorder that is visible and it usually develops gradually. Hence, it is often not recognized or considered to be a problem by employees. Many people perceive their hearing impairment as part of themselves and are therefore not alarmed by it. The employees who do recognize the problem of their hearing impairment may not report it, because of shame or the fear for stigma [8]. It may therefore be difficult to measure a difference in effect (i.e., 'need for recovery after work') between the intervention and control group. Another limitation of this study is that it is not possible to blind the employees and multidisciplinary team to the intervention. Selection bias is possible because of self selection of companies participating in this type of studies. It may be expected that only companies in which hearing impairment is considered as an important health condition, for example because of knowledge about risk of noise, will participate in this study. It may also be argued that only companies that recognise the importance of preventive interventions participate. For two of the participating companies (airline and steel industry), this may have influenced their decision to participate. However, for the university, hearing protection is less of an issue. Hence, it is argued that the participating companies represent a good mix of employers.

### Policy implications

This VEP integrated care programme is a promising way to help reducing work disability and the burden for hearing impaired employees. If this study will prove its effectiveness, the VEP integrated care programme can foster the maintenance, and improvement in the well-being of employees with hearing impairment by facilitating and retention of their work through the VEP broadly. When proven cost-effective from the company perspective, it can be considered as a useful intervention in other occupational health care settings to prevent disabilities for hearing impaired employees. Furthermore, if cost-effective from the societal perspective, it will be worth considering inclusion of the VEP integrated programme in the basic package of social insurances. It is expected that the results of this study will become available in 2014.

## Abbreviations

ASE: attitude, social influence and self-efficacy; BCA: bias corrected and accelerated bootstrapping; CE: cost-effectiveness; CEAC: cost-effectiveness acceptability curves; CPHI: communication profile for the hearing impaired questionnaire; dB: decibel; dB SNR: decibel signal-to-noise ratio; EMP: employer; ENT: ear nose and throat; GP: general practitioner; GSES: general self-efficacy scale; HDS: hearing and distress screener; ICER: incremental cost-effectiveness ratio; ICF: international classification of functioning: disability and health; JCQ: job content questionnaire; JDC: job demand control; MICE: multivariate imputation by chained equations method; NFR: need for recovery; NVAB: Dutch board for occupational medicine; OHS: occupational health services; OP: occupational physician; PHS: periodical health screening; PRODISQ: productivity and disease questionnaire; PSQOH: patient satisfaction with occupational health services questionnaire; SNR: signal to noise ratio; SRT: speech reception threshold; VAS: visual analogue scale; VEP: vocational enablement protocol; WHO: World Health Organization; 4DSQ: four dimensional symptom questionnaire.
